### Background

1.1

More than 80% of venous leg ulcers may be colonized or infected by bacteria (O’Meara et al., 2014). One of the leading causes of delay in the healing is the presence of pathogenic bioburden. In fact, bacterial biofilms (exopolysaccharides extracellular matrix which provides structural bacterial defence) over the wound have been associated with chronic wound interference recovery (Clinton & Carter, 2015; Gompelman, van Asten, & Peters, 2016; Hurlow et al., 2015). Moreover, biofilm provides a key resistance to local and systemic antibiotic treatments, especially in the case of venous ulcers (Bianchi et al., 2016). Major representative strains are *Staphylococcus aureus* and *Pseudomonas aeruginosa*, while it can be also found in anaerobic microorganisms (*Peptostreptococcus* species and gram‐negative *Bacillus*), *Enterobacteria,* or group A *Streptococcus* (Etchebarne et al., 2017).

The presence of colonization or infection in chronic wounds produces a direct effect in their healing and recovery when colony‐forming units (CFUs) exceed 10^5^ per tissue gram. Thus, wound colonization by pathogenic bacteria promotes its chronification. Furthermore, pathogenic bacteria can also generates intra‐wound synergistic effects with other non‐pathogenic microorganisms increasing their action (Rahim et al., 2017).

This problem has been usually addressed by using local dressings, with the aim to reduce the total wound bacterial load. Although the most common therapeutic strategy is the use of silver dressings due to their antimicrobial effect, there is a lack of evidence about their effectiveness in venous ulcers (O’Meara et al., 2014). Moreover, there is some uncertainty over adverse effects derived from systemic absorption of silver molecules, in addition to generate silver resistance in many bacteria strains (Maillard & Hartemann, 2013; Mijnendonckx, Leys, Mahillon, Silver, & Van Houdt, 2013; Percival et al., 2008). Additionally, these inconveniences can involve an elevated cost when long‐term treatments are needed.

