#### Design

2.2.1

An open, randomized, controlled trial with blinded evaluators will be carried out.

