#### Allocation

2.2.3

Inclusion of participants will be randomized in a concealed sequence to participants, clinical nurses, and investigators. Once a participant meets the inclusion criteria, collaborative investigators will know by means of a telephone call the study group assigned according to the random sequence. The random sequence will be generated by a computerized system. Although the study groups are not blinded for patients and nurses, the members of the team who will carry out the analyses will be blinded to the allocation groups.

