##### Secondary outcome measures

Wound size will be evaluated by planimetry using PictZar^®^ 7.6.1 software (Wendelken et al., 2011). Photos will be taken from affected area completely in parallel with respect to the ulcer and the photo will have to include a calibrated rule of 3 cm (standardized procedure according to PictZar^®^ planimetry). The characteristics and clinical evolution of the wound will be evaluated using the Resvech 2.0 scale (Restrepo‐Medrano & Verdú Soriano, 2011).

Healing time will be measured by the number of days until complete healing. This outcome will be complied if re‐epithelialization of the skin is confirmed in two consecutive visits across 2 weeks. Pain will be measured using the Numerical Rating Scale (NRS).

Health‐related quality of life will be measured by means of the Charing Cross Venous Ulcer Questionnaire (CCVUQ) (González de la Torre, Quintana‐Lorenzo, Perdomo‐Pérez, & Verdú, 2017; González‐Consuegra & Verdú, 2010). Adverse events related to the treatment will be collected both by nurses and patients. Follow‐up will be carried out at 4, 8, and 12 weeks, except the quality of life, which will be only evaluated at baseline and 12 weeks. Adherence to the treatment will be checked with the nurse and with the evaluation of consumed dressings.

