#### Ethical considerations

2.2.8

The study has been approved by the Ethics and Research Committee of Malaga. The study will meet the requirements of Helsinki Statement and later revisions and the principles of good clinical practices. Informed consent will be demanded to the participants in accordance with current law in Spain by using an application form and an information sheet designed for this purpose. Due to the characteristics of the target study population, it is possible to find patients with presence of cognitive impairment. In those cases, informed consent will be requested from their caregivers.

The Ethics and Research Committee of Malaga will be reported in advance on any modification in the eligibility criteria, outcomes, or analyses. All the monitoring procedure of adverse effects will be driven by the regulation referred to MEDDEV 2.7/3 Guide Review 3 “Clinical investigations: Serious adverse event reporting under Directives 90/385/EEC and 93/42/EEC” and by the ISO regulation number 14155:2012. All the participants potential harms will be covered by an insurance policy issued for the trial. This trial is registered at Clinical Trials (NCT03667937).

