#### Validity and reliability

2.2.9

According to ISO 14971 regulation, several procedures have been set to manage potential risk due to the use of the study products. Scientific literature has been extensively reviewed about risks of Cutimed Sorbact^®^ dressings, with no adverse effects reported to date (Totty et al., 2017).

A key strength of this study is that it will be performed under routine clinical conditions, in multiple centres, both in Primary Health Care and nursing homes. This feature will give a strong external validity. In addition, the use of planimetry software PictZar^®^ ensures objectivity to evaluate the wound area.

The trial will be supervised by an independent monitoring committee integrated by external members belonging to the District of Primary Health Care of Málaga and IBIMA. This committee will carry out audits each 6 months. On the other hand, some potential confounding variables will be recorded such as antibiotic and/or analgesic therapy, nutritional status, and level of dependence (Barthel index). Moreover, this trial will comply with a rigorous procedure to report adverse events, to avoid the usual lack of reporting adverse events in venous leg ulcer research (Jull & Biggs, 2019).

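### The safety outcome is defined by relatedness to treatment and collected by unblinded nurses and patients, so the arms could differ through attribution alone

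*Protocol article*

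**What the plan says.** All references are to the protocol article.

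- **Secondary outcome measures (within 2.2.5)** has the only sentence that defines the safety outcome: "Adverse events related to the treatment will be collected both by nurses and patients".
- **Allocation (2.2.3)**: "Although the study groups are not blinded for patients and nurses", it continues, "the members of the team who will carry out the analyses will be blinded to the allocation groups".
- **Design (2.2.1)**: "An open, randomized, controlled trial with blinded evaluators will be carried out". The evaluators are given no role in safety.
- **Aim (2.1)** lists evaluation of the test dressing's safety alongside the secondary aims.
- **Ethical considerations (2.2.8)** places adverse effect monitoring under a European device guide, whose title includes "Serious adverse event reporting under Directives 90/385/EEC and 93/42/EEC", and under ISO 14155:2012.
- **Validity and reliability (2.2.9)** promises a rigorous adverse event reporting procedure, meant to avoid the under-reporting common in this field. It also describes the literature on the test dressing as "with no adverse effects reported to date".
- **Background (1.1)** says of the comparator's active agent that "there is some uncertainty over adverse effects derived from systemic absorption of silver molecules".

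**The concern.** Relatedness is usually a classification applied to an event already on the form. Here it is part of what is collected. An event that nobody links to the dressing has no stated route into the adverse event data, and both named collectors know which dressing was used.

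If the readiness to link an event to the dressing differs by arm, the recorded rates differ even when the true rates are equal. The article shows what the trial team expects: a clean record for the test dressing and open questions about silver. If staff share that expectation, the distortion would favour the test dressing.

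At stake is a stated aim. The Discussion also makes its hoped-for benefit conditional on lower colonization without adverse events. Blinding the analysts does not help, because the filter acts before the data reach them, and an analysis plan cannot restore events that were never written down.

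**Working it through.** The article gives no adverse event rate and no figure for the safety outcome, so there is nothing to reproduce. The check is mainly a comparison of sections, followed by an illustration on assumed inputs.

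**Sections side by side**

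1. *What is collected?* Events related to the treatment (Secondary outcome measures). No other section says that events are recorded whatever their cause.
2. *Who collects?* Nurses and patients (same sentence). Both are unblinded (Allocation).
3. *Who judges relatedness?* Not stated.
4. *Is there a blinded review of causality?* None is stated. The analysts are blinded, and the blinded evaluators mentioned under Design have no safety role.
5. *Does another section override the filter?* The guide cited under Ethical considerations is, by its title, about serious events. The ISO standard cited with it is not described there as limited to serious events, but its content is not in the article, so it neither confirms nor refutes wider capture. Validity and reliability promises rigour without saying which events are captured. Neither section restricts collection to related events, and neither states that all are collected.
6. *What escapes the filter?* Pain (numerical rating scale) and wound characteristics and evolution (Resvech 2.0) are measured at follow-up regardless of attribution. Clinical deterioration is a dropout criterion with no relatedness condition (Intervention). Antibiotic and analgesic therapy are recorded (Validity and reliability).

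**Illustration of the mechanism**

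Inputs: 204 participants (Sample), hence 204 / 2 = 102 per arm, taking equal arms. Assumed: a true event rate *r*, the same in both arms, and shares *a*T and *a*C of events called related in the test and control arms.

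Recorded rate = *r* × *a*. The recorded rate ratio is (*r* × *a*T) / (*r* × *a*C) = *a*T / *a*C, so it does not depend on *r*. The last column is the approximate chance of a nominally significant difference (two-sided 5%, normal approximation, rough where counts are small).

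| *r* | *a*T v *a*C | Recorded rates | False difference (points) | Ratio | Chance of p < 0.05 |
|---|---|---|---|---|---|
| 10% | 40% v 60% | 4% v 6% | 2 | 0.67 | 10% |
| 20% | 40% v 60% | 8% v 12% | 4 | 0.67 | 16% |
| 40% | 40% v 60% | 16% v 24% | 8 | 0.67 | 30% |
| 10% | 30% v 70% | 3% v 7% | 4 | 0.43 | 26% |
| 20% | 30% v 70% | 6% v 14% | 8 | 0.43 | 48% |
| 40% | 30% v 70% | 12% v 28% | 16 | 0.43 | 82% |

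A case with lower attribution, at *r* = 20%:

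- Test 10%, control 30%: 102 × 0.20 × 0.10 = 2.0 against 102 × 0.20 × 0.30 = 6.1 events, ratio 0.33. Fisher's exact test on 2/102 against 6/102 gives two-sided p = 0.28.
- Test 15%, control 30%: 102 × 0.20 × 0.15 = 3.1 against 6.1 events, ratio 0.5. On 3/102 against 6/102, p = 0.50.

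If every event is recorded, *a* = 1 in both arms, the ratio is 1, and attribution alone creates no difference.

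**The case against.** The strongest case on the other side has five parts.

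- **The text says less than a reader might infer.** One could take it that *only* related events are recorded and that nurses and patients themselves decide relatedness. Neither is stated: the sentence does not say that other events go unrecorded, and it says that nurses and patients collect events, not that they judge cause. This stands. The point rests on the sentence as worded and on the absence of a named judge.
- **The device guide and ISO standard may require full capture.** They may. Their content is not in the article, so they cannot be counted for either side. What can be said is that the visible text does not override the outcome definition.
- **This is a condensed article.** The event form and the causality assessor may well be in the full protocol, and their absence here is not in itself a fault. That covers missing detail. It does not cover a collection rule that the article does state and that would cause bias if followed.
- **Much local harm is caught elsewhere.** This stands for pain and wound evolution, and partly for deterioration and antibiotic use. It narrows the exposure without removing it.
- **The size is invented and the comparison is not pre-specified.** The rates are assumptions, and in the low-attribution case the differences would not reach significance. Data analysis names no between-arm safety test. Both points are fair, so no ratio above should be read as an estimate. A descriptive table by arm would still carry the distortion.

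A reader might also infer that the staff are told to expect harm from silver and none from the test dressing. The article does not support that. Those remarks are in the Background and in an account of a literature review, and nothing says they are given to nurses or patients as instructions.

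**Conclusion.** The concern holds in a limited form. As worded, the safety outcome makes relatedness a condition of collection. Its collectors know the arm, and no judge of relatedness or blinded causality review is stated. Differences between arms could therefore arise from attribution alone, in an outcome that serves a stated aim. The wording also needs to be reconciled with the article's own sections on adverse event procedures.

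The exposure is mainly local and systemic events other than pain and wound evolution. Its size cannot be established: the ratios of 0.33 to 0.67 follow entirely from assumed attribution shares. The direction is also uncertain. It would favour the test dressing only if staff share the expectations in the article. The documents do not support a conclusion that the safety results will be wrong, or that unrelated events will certainly be lost. They do support correcting the sentence, because the change is cheap and an event screened out of the adverse event record cannot be put back at analysis.

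**What to change.** Reword the adverse event sentence under Secondary outcome measures, and align Ethical considerations and Validity and reliability with it, so that:

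1. all adverse events are recorded in both arms whatever their presumed cause;
2. relatedness is a separate field on the form, with the person who judges it named, and judged blinded to arm where existing staff allow;
3. the main safety summary is all adverse events by arm, with related events as a supporting table.

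The cost is a sentence of text, a field on the event form, somewhat more recording by nurses, and more background events in the tables. The routine dressing appointments, no more than 72 hours apart (Intervention), already give the occasion to ask.

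The change removes the relatedness filter. It does not remove differences between arms in how readily unblinded nurses and patients notice or report events, and the trial report should say so.

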**Methods:**

Patients with chronic venous leg ulcers with signs of critical colonization will be randomized in a concealed sequence using computer software to receive one of the alternative dressings. A total of 204 participants recruited in Primary Health Care and nursing homes will be necessary to assure statistical power. Measures will include sociodemographic variables, wound‐related variables (area, exudate, and time to healing), level of pain, adverse effects, and health‐related quality of life. Smear samples will be collected from the ulcers and will be subject to DNA‐typing technique through polymerase chain reaction to obtain the level of colony‐forming units. Measures will be collected at baseline, 4, 8, and 12 weeks.

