#### Intervention

2.2.6

Following the obtention of the baseline data, the nurse who usually gives care to the patient will proceed to cure the venous ulcer using a standardized procedure. They will wash the area with saline solution and evaluate if mechanical debridement is necessary. Following, they will apply Cutimed Sorbact^®^ dressing (intervention) or Aquacel^®^ Ag Extra (control) dressings in the wound. Finally, they will cover the wound with a secondary gauze dressing and a double compression bandage. Patient's appointments will not extend beyond 72 hr, although depending on the level of exudate and the status of the wound, the nurse may decide to shorten this interval.

Dropout criteria are as follows: (a) Local or systemic clinical deterioration that indicates that continuation at the study is not appropriate; (b) Lack of patient's concordance; (c) Withdrawal of patient consent; and (d) Complete healing before week 12. The data collection period comprehends from May 2012 to December 2020.

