#### Data analysis

2.2.7

Data analysis will include descriptive statistics and exploratory analysis to determine the normality of the distributions and to check the range of data values. Bivariant analysis will be performed by chi‐square test, Student *t* test, Mann–Whitney U, Wilcoxon W, ANOVA, and Kruskal–Wallis test, depending on the normality of the distributions, type of variable analysed, and their homoscedasticity, which will be tested by the Levene's test. Intra‐group analysis will be performed by general linear models, with the corresponding corrections in multiple comparisons by Bonferroni test. To test the null hypothesis (inter‐group analysis), lineal generalized models will be developed in repeated measures, taking on consideration CFUs number as dependent variable as well as control or experimental designation group as a factor. Even if basal differences are significative, they will be attached as adjustment factor, following Mallinckrodt and Lipkovich recommendations (Mallinckrodt, Lipkovich, & Lipkovich, 2016). Sphericity will be tested using Mauchly test, Greenhouse‐Geisser test, or Huynh‐Feldt test in case of no setting.

All analyses will be performed by an intention‐to‐treat approach. To this purpose, missing data will be calculated by multiple imputation methods.

All the analyses will be performed in a blinded way.

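### The only CCVUQ score after baseline is at week 12, but patients who heal earlier are classed as dropouts, so quality of life goes missing because of the outcome

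*Protocol article*

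**What the plan says.** Quality of life is a named secondary endpoint (Abstract, Aim; section 2.1). It is measured with the CCVUQ. Under Secondary outcome measures the general rule is "Follow‐up will be carried out at 4, 8, and 12 weeks", with the exception "except the quality of life, which will be only evaluated at baseline and 12 weeks". Pain and wound measures follow the general rule; the CCVUQ has one planned value after baseline.

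Section 2.2.6 (Intervention) lists four dropout criteria. The first three are a worsening that makes staying in the trial unsuitable, poor adherence by the patient, and revoked consent. The fourth reads "d) Complete healing before week 12". Only the last carries a stated time. The article mentions no questionnaire at exit and none at week 12 for a patient who has left.

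Section 2.2.7 (Data analysis) applies intention to treat to all analyses and says that "missing data will be calculated by multiple imputation methods". It does not name the imputation variables.

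The Abstract (Methods) includes quality of life in its list of measures and then states: "Measures will be collected at baseline, 4, 8, and 12 weeks". It leaves out the exception made in the body.

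**The concern.** Three stated rules meet badly: a single late assessment, an exit triggered by success, and imputation of whatever is then absent. A patient confirmed healed at week 7, say, leaves the study five weeks before the only follow-up CCVUQ. That score is missing because of the treatment outcome, and missing more often in whichever arm heals faster.

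This touches the benefit that the trial hopes to show. The Discussion (section 3) expects lower colonization to shorten healing and says that the trial will be able to assess the effect on quality of life. If part of any gain runs through healing, the patients who carry it are those without a score. An estimate built mostly on ulcers not confirmed healed would understate that part.

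**Working it through.** The documents give no target difference, standard deviation or power for quality of life, and no healing rate. There is no plan figure to reproduce. The check sets out who would be scored, then sizes the possible loss on assumed figures.

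**Step 1. Which CCVUQ scores exist if the text is followed as written**

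| Patient | Baseline | After baseline |
|---|---|---|
| Healing confirmed before week 12 | yes | none provided for |
| Wound closes after about week 10 | yes | week 12 |
| Ulcer open at week 12, still in study | yes | week 12 |
| Leaves before week 12 for another listed reason | yes | none provided for |

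The second row follows from the healing definition under Secondary outcome measures, which needs confirmation at two consecutive visits across 2 weeks. Since 12 − 2 = 10, a wound that first closes after about week 10 is not confirmed before week 12, and the patient stays in.

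**Step 2. How many patients**

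Section 2.2.2 raises 186 to 204 for dropouts, an allowance of 18, and 18/204 = 8.8%. Early healing alone uses this up once 8.8% of patients heal. If healed patients leave unscored, the most that can have a week-12 score is 204 × (1 − h), where h is an assumed overall early-healing rate:

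- h = 20%: 163
- h = 30%: 143
- h = 40%: 122

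**Step 3. Size of the possible bias**

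Let p₁ and p₂ be the proportions healed before week 12 in the two arms, and g the difference in mean CCVUQ improvement between healed and unhealed patients. Take g as equal in both arms, with no effect on quality of life other than through healing. Then

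true difference = (p₁ − p₂) × g.

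If every healed patient is imputed at the unhealed mean, both arms average the same and the expected estimate is 0. The loss is then the full (p₁ − p₂) × g.

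Assumed inputs: improvement of 20 points if healed and 5 if not (g = 15), SD 18, 102 per arm (204/2).

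- SE = 18 × √(2/102) = 2.52 points.
- 40% v 20%: (0.40 × 20 + 0.60 × 5) − (0.20 × 20 + 0.80 × 5) = 11.0 − 8.0 = 3.0 points; 3.0/2.52 = 1.2 SE.
- 30% v 20%: 9.5 − 8.0 = 1.5 points; 1.5/2.52 = 0.6 SE.
- 40% v 30% with g = 5: 0.10 × 5 = 0.5 points; 0.5/2.52 = 0.2 SE.
- Equal healing in both arms: 0.

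These are upper bounds for each set of inputs. If the imputation recovers a share r of the healed–unhealed gap, the loss is (1 − r) × (p₁ − p₂) × g. With r = 0.5 the first case falls from 3.0 to 1.5 points.

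**Step 4. What the imputation can draw on**

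Baseline CCVUQ, pain, wound size and the wound scale up to exit, and healing status are all available as predictors. But the link between confirmed healing and the week-12 CCVUQ has to be estimated from patients who have both, and as written there are few or none. Late-closing wounds help in part, although they have been closed for a shorter time than those that healed early.

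**The case against.** The strongest defence is that measuring a secondary patient-reported outcome at baseline and at the end is an ordinary design choice, openly stated. That stands: the schedule alone is no error. The difficulty comes from pairing it with exit on healing.

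A reader might infer more than the text supports:

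- *That nobody who leaves early can be scored.* The article neither provides for nor forbids a week-12 questionnaire after exit, and a condensed article may leave exit procedures to the full protocol. Only the healing criterion carries a time; for the other three, exit before week 12 is implied at most. What goes beyond missing detail is that a success is labelled a dropout while its score falls due later.
- *That the imputation has nothing to work with.* It lacks a CCVUQ value between baseline and week 12, but has other interim measures and some closed wounds scored at week 12.
- *That the whole effect is lost.* This is the worst case on assumed gains, SD and healing rates, for an endpoint for which no power is claimed.
- *That the abstract contradicts the body in a serious way.* Its list also includes sociodemographic variables and time to healing, which would not be repeated at every visit. It is a summary that omits an exception, and needs only a wording correction.

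It is also fair to say that CCVUQ scores at weeks 4 and 8 would not cure the problem: for a patient who heals later they describe an open ulcer.

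**Conclusion.** The point holds in a limited form. As written, patients confirmed healed before week 12 lose their only CCVUQ score after baseline because of the outcome, and the imputation must extrapolate mainly from ulcers not confirmed healed. If the arms heal at different rates and healing improves quality of life, the estimated difference can be pulled toward zero. On the assumed figures the loss is at most 3.0 points (1.2 SE) at 40% v 20% healed, at most 1.5 points (0.6 SE) at 30% v 20%, and nil if the arms heal equally. None of these rates, gains or SDs is in the documents. The effect is on a named secondary endpoint. It is worth correcting because the correction is cheap.

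**What to change.** Amend Secondary outcome measures so that:

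1. the CCVUQ is also completed at the last study visit of any patient who leaves early, where consent allows;
2. the CCVUQ is still collected at week 12 from all randomised patients who have not withdrawn consent, including those who healed or stopped treatment.

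State in section 2.2.7 that both scores, together with healing status, are used in the quality-of-life analysis and in the imputation model. The week-12 score remains the endpoint; the exit score supports imputation where week 12 is still missing. Scores at weeks 4 and 8 for everyone are optional.

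Align the schedule in the Abstract (Methods) with the body by naming the quality-of-life exception.

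This changes data collection only and leaves the clinical exit criteria as they are. The cost is one short extra questionnaire per affected patient and a week-12 contact with patients who have already left. Appointments under section 2.2.6 are at most 72 hours apart and healing has to be confirmed at a visit, so the exit score of a healed patient needs no extra attendance.
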